At months 4, 8, 12, 16, 20, and 24. During phone surveys after baseline data collection, patients will complete a 120-day TLFB [54] to document their illicit opioid and other nonprescribed drug and alcohol use as well as health service use during the past 4 months. Health service use will be collected for the categories listed under “Health service use and cost” below. Patients will also complete measures of: relapse risk (Brief Addiction Monitor [55], nine items); pain severity (NRS scale [56], one item); HIV/HCV screening and link-to-care status (testing status and if tested, result, and if positive, whether the patient saw a medical provider); risk behaviors (HRBS [57], five items); status of current housing (two items) and employment (three items on type of employment, hours worked); quality of life (The Satisfaction with Life Scale [58], eight items); rating scale for withdrawal (three items); self-reported medication adherence (Morisky Medication Adherence Scale: MMAS-4 [59], four items); and loneliness (three items). We will collect number of phones lost, stolen, or broken (research records). For retention in treatment, we will take the proportion of appointments attended from clinic records. We will also determine if participants are engaging in other forms of treatment outside of the treatment facility, such as seeing a therapist, working with a sponsor, or attending NA/AA meetings.

Mediators. Self-determination theory (SDT) constructs will be assessed as follows: autonomy, Treatment Self-Regulation Questionnaire [60] (six items); competence, revised Drug-Taking Confidence Questionnaire [61] (eight items); and relatedness, our own bonding scale (five items). Negative affect will be assessed by Positive and Negative Affect: PANAS [62, 63] (20 items), and self-stigma by the self-devaluation subscale of the self-stigma in substance abuse scale [64] (seven items).

Moderators: we will focus our evaluation on gender but also collect data on other potential moderators (SUD severity as determined by the treatment site at intake using DSM-V criteria, pain as determined by the NRS-11, withdrawal, and loneliness).

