### Data analysis

#### Power and sample size justification

Primary analysis. Our study will be powered to detect a difference between MAT + A-CHESS and MAT in percentage of days using illicit opioids across the 24-month intervention period. Based on data from the two sites from which most study participants will be recruited, we assume 35% attrition over the course of the study, providing an *N* of 286. Using the power program by Hedeker et al. [69] and assuming up to cubic trends in the data, given expected attrition, recruitment of 440 patients will provide 80% power to uncover a standardized difference of .35 across the 24 months. From prior data [70, 71], this would be a difference of approximately three opioid use days/month depending on the observed standard deviation.

Secondary analyses. Power for examining intervention effects for the secondary outcomes would be similar as for the percentage of opioid use days, though the difference implied by the standardized difference of .35 will depend on the actual standard deviation of each measure. For secondary outcomes related to HIV and HCV, the sample size also provides 80% power to find a two-tailed difference in proportion screened for HIV/HCV of 16% [72] (conservatively assuming that screening for one group nears 50%, the point requiring the largest difference to achieve a specified power).

Mediation and moderation analyses. Power for detecting specific parameter changes in the structural model will be estimated using a procedure proposed by Satorra and Saris [73] that approximates the noncentral chi-square distribution. A total *N* of approximately 220 patients would provide adequate power (>.80) to detect a group difference in a parameter by 0.4 standard deviations (a moderate effect). Since our primary analysis projects a final *N* of 286, we are confident our secondary process analysis will have adequate power.

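### The adequate-power statement for moderation matches a two-group contrast; a treatment-by-gender interaction of the same 0.4 SD has about 34% to 39% power at 286 patients, before any repeated-measures gain

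*Protocol article*

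**What the plan says.** In the Protocol article, Power and sample size justification, one paragraph headed Mediation and moderation analyses covers both kinds of process analysis. Power is to be found "using a procedure proposed by Satorra and Saris [73] that approximates the noncentral chi-square distribution". A total of about 220 "patients would provide adequate power (>.80) to detect a group difference in a parameter by 0.4 standard deviations (a moderate effect"). Because the primary analysis projects 286 patients at the end, the paragraph closes: "we are confident our secondary process analysis will have adequate power". It shows no separate calculation for an interaction.

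The 286 comes from the primary-analysis paragraph of the same section, where "we assume 35% attrition over the course of the study" and 440 are recruited.

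Moderation is a declared aim. Study design, hypotheses, and outcomes says the study will determine which person-level factors change the effect of adding A-CHESS. The Moderators paragraph of Measures says "we will focus our evaluation on gender but also collect data on other potential moderators". Randomization is 1:1 and stratified on gender.

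**The concern.** A moderator is tested by comparing two treatment effects, here the effect in women and the effect in men. With equal gender groups, that difference has four times the variance of the overall comparison between arms, and more if the split is uneven. A sample size that suffices for a two-group difference of 0.4 SD is therefore far from sufficient for a 0.4 SD difference between two treatment effects.

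The paragraph's heading names moderation and its last sentence claims adequate power without separating the two kinds of analysis. A reader of the results would take the gender interaction to have been tested with more than 80% power. If the test is then non-significant, that published assurance invites more weight on the null result than the design can bear.

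**Working it through.** **Inputs from the protocol:** effect 0.4 SD; N = 220 said to suffice; projected N = 440 × 0.65 = 286; 1:1 allocation; gender as lead moderator; six follow-up surveys.

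**Assumptions, because the protocol does not give them:** two-sided alpha of 0.05; gender split from 50/50 to 70/30; 0.4 SD measured on the outcome-SD scale, which is the scale on which the stated figure reproduces.

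**Step 1: reproduce the stated figure as a two-group contrast.** In SD units, SE = sqrt(4/N) and power = Φ(0.4/SE − 1.96).
- N = 220: SE = 0.1348, power = Φ(2.967 − 1.96) = 84%. A noncentral chi-square with 1 df, the distribution the protocol names, gives 84.3%; a t-test gives 84.0%.
- N = 198 is enough for 80%.
- N = 286: SE = 0.1183, power = 92%.

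So the claim of more than 80% at about 220 is right for a two-group contrast.

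**Step 2: treatment-by-gender interaction of 0.4 SD.** With share p in one gender, SE = sqrt(4/(N·p·(1 − p))).

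| N | Gender split | SE | Power |
|---|---|---|---|
| 220 | 50/50 | 0.2697 | 32% |
| 286 | 50/50 | 0.2365 | 39% |
| 286 | 65/35 | 0.2479 | 36% |
| 286 | 70/30 | 0.2581 | 34% |

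For the second row: Φ(0.4/0.2365 − 1.96) = Φ(−0.27) = 39%. A simulation of that row (4,000 runs) gave 40%.

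**Step 3: what 80% power would take.** The multiplier is 1.96 + 0.84 = 2.80.
- Detectable interaction at N = 286: 2.80 × 0.2365 = 0.66 SD at 50/50; 2.80 × 0.2581 = 0.72 SD at 70/30.
- Patients needed for 0.4 SD: about 785 analysed at 50/50, about 934 at 70/30.

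**Step 4: allow for repeated measures.** Averaging six measures with intraclass correlation ρ multiplies the SE by sqrt((1 + 5ρ)/6), which is 0.764 at ρ = 0.5 and 0.866 at ρ = 0.7. Both values of ρ are assumed. With an even split:

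| N | ρ = 0.5 | ρ = 0.7 |
|---|---|---|
| 286 | SE 0.1807, power 60% | SE 0.2048, power 50% |
| 440 (no loss at all) | SE 0.1456, power 78% | SE 0.1651, power 68% |

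**Step 5: compare with the protocol's own primary calculation.** It says that "recruitment of 440 patients will provide 80% power to uncover a standardized difference of .35 across the 24 months". A plain two-group formula at 286 gives 84% for 0.35 SD, so the stated 80% contains no visible repeated-measures gain. Calibrated to it, the two-arm SE is 0.35/2.80 = 0.125 and the interaction SE is twice that, 0.250. Power for a 0.4 SD interaction is then Φ(0.4/0.250 − 1.96) = 36%, inside the range of Step 2.

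**The case against.** The strongest reply is that the protocol never describes a two-arm comparison of means here. It speaks of parameter changes in a structural model, and in a multi-group structural model a path that differs between groups is itself a form of moderation. The terms group and parameter, and the scale of the 0.4 SD, are left undefined. The match in Step 1 is also loose: any N from 198 upwards gives at least 80%. This stands. The two-group reading is inferred from a numerical match and is not stated in the text. It does not rescue the sentence, however. If the groups are arms, moderation is not addressed. If they are genders and the parameter is the treatment effect in outcome-SD units, power at 220 is 32%.

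A second reply is that the planned mixed-effects analysis can use partial follow-up from more than 286 patients, so Step 2 may be too pessimistic. That is possible, which is why Step 4 is shown. But the protocol gives no correlation, and reaching 80% at 286 would require repeated measures or covariates to remove about 64% of the outcome variance. Even six complete measures on all 440 patients reach only 68% to 78% under the assumed correlations. A crossover interaction of 0.8 SD (0.4 SD in opposite directions in men and women) would have 92% power, but the protocol proposes no such effect.

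A reader might also infer that the protocol intends to treat a non-significant interaction as proof of equal effect. It does not say so; that is a risk created by the power statement. Moderation carries no directional hypothesis, and the Discussion describes it as exploring for whom A-CHESS works. A reader might likewise extend the percentages to pain, withdrawal, loneliness and severity. The formula used here is for a two-level moderator, and no calculation was made for those measures.

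**Conclusion.** As written, the paragraph claims adequate power for a declared aim, and the figure it cites does not support that claim for a gender interaction of the stated size. At the projected 286 patients, power for a 0.4 SD treatment-by-gender interaction is about 39% with an even split and 34% at 70/30, and the detectable interaction is about 0.66 to 0.72 SD. These figures assume two-sided 0.05, the outcome-SD scale, and no gain from repeated measures or covariates. With an assumed gain from six measures and an even split, power is 50% to 60%.

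Quoting 50% to 60% as the design's power would go too far, because it rests on correlations the protocol does not give. What holds across the scenarios tried is that a 0.4 SD gender interaction stays below 80%. The point concerns a secondary aim. It says nothing against the primary sample size and does not show that the mediation analyses are underpowered.

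**What to change.** Limit the adequate-power sentence to the two-group parameter it covers, and say what the groups, the parameter and the SD scale are. For the gender-by-treatment interaction, state the power (about 34% to 39% for 0.4 SD at 286 patients without a repeated-measures gain) and the detectable interaction (about 0.66 to 0.72 SD), with the assumed gender mix and alpha. If a gain from repeated measures is claimed, show it under a stated correlation. Present moderation as interaction estimates with 95% intervals and make no claim of adequate power for it.

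The cost is a less favourable figure in the text. No extra patients are needed, and the primary sample size does not change.

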### Interventions

#### Control condition: MAT

Patients in the control condition will receive treatment as usual including MAT. Treatment could consist of a recovery plan, medication, and regularly scheduled behavioral interventions such as monthly group counseling sessions, sessions with a substance abuse counselor, and Narcotics Anonymous/Alcoholics Anonymous (NA/AA) meetings. Medication may include methadone, injectable naltrexone, or buprenorphine. The sequence and duration of medication and behavioral interventions will vary by patient and site. Discussions with sites revealed that we should not try to control variations because they are tailored to individual patients. We will document which medications are used and will include as covariates when and how medications change between the 4-month surveys.

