Triage and feedback functionality is designed to derail the relapse process, giving the patient just-in-time, tailored coping support. A-CHESS will be customized at the start by each patient to set options that will be triggered in a moment of need. For example, if a patient reports a craving triggered by environmental cues, such as seeing someone else use, A-CHESS might remind the patient of relaxation exercises, connect them to online peer support and the healthy events calendar, and/or notify a counselor, who may initiate contact via text or private message. Participants whose patterns of using A-CHESS demonstrate they are likely to stop using the system will receive automated messages and tailored messages from coaches to encourage them to reengage.

The counselor dashboard [43], developed by addiction physicians and psychologists, harvests clinically relevant data from A-CHESS and presents it to counselors to help them quickly: (1) identify patients who may be at high risk for relapse and/or benefit from clinical intervention, (2) see a detailed analysis of a patient’s recent history, e.g., trends in individual BAM items, A-CHESS use, and relapse data, and (3) intervene with patients (e.g., through texting in A-CHESS). When a counselor logs into the counselor dashboard, he sees ‘red pins’ generated when A-CHESS (using counselor-determined priorities) detects that a patient may be at high risk. The counselor can adjust the cutoffs for red pins so the ones he sees are most useful.

HIV/HCV services. A-CHESS will integrate components of our team’s existing computerized risk reduction systems that collect data on patients’ HIV/HCV risk behaviors and deliver behavior change interventions tailored to the patient’s self-reported readiness for change. At enrollment, participants in both study conditions will be asked if they have been screened for HIV and HCV. Patients who test negative or decline testing at baseline will be sent reminders from A-CHESS about future testing at a frequency based on reported risk behaviors. Patients found to be HIV or HCV-positive will be provided with targeted multimedia health education content, access to online resources, and location-specific links to clinical care and case management.

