### Smartphone distribution

Patients randomized to MAT + A-CHESS who do not already have an Android smartphone will be given one loaded with A-CHESS, along with a data plan that includes unlimited data, text, and voice for 16 months. Patients who already have an Android smartphone will have A-CHESS installed on their phone. We will provide up to one replacement phone to patients who report their phone lost, stolen, or broken. If patients lose the second phone, we will offer to load A-CHESS onto an appropriate replacement smartphone (e.g., Samsung S5) that they obtain. We have included in the budget a 20% allowance for replacement phones, which has proven sufficient in prior CHESS research, including trials with populations of addicted patients [33, 46].

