A-CHESS use. A-CHESS use will be collected in time-stamped log files and includes when a patient accessed A-CHESS, service(s) selected, duration of service use, pages viewed, messages posted versus received, and communication style and content of messages. Content will be subject to computer-automated content analysis to identify communication styles that may predict study outcomes. Cumulative use (number of pages viewed and days used) significantly predicted risky drinking days in the randomized trial of A-CHESS with alcohol-dependent patients [33]. We will also collect data on sources of other SUD-related information and support.

Health service use and cost. Our cost analysis is motivated by the potential that A-CHESS has shown to reduce the use of costly health services associated with relapse. (In a field test with US military veterans, A-CHESS users had substantially decreased rehospitalizations related to relapse.) Our approach to measuring and analyzing health use data is adapted from McCollister and French’s 2003 analysis of the economic benefit of addiction interventions [65]. We will use the following categories of health service use: emergency room visits, hospital detox (day), and short-term residential treatment (day). We will also track costs for all other hospital visits and stays (in addition to emergency room visits and hospital detox); urgent care visits for any reason (to which we will apply cost estimates derived from a national survey of urgent care clinics [66]; individual psychotherapy or psychiatric care; and self-reported outpatient addiction treatment services after relapse (using the categories of outpatient addiction care outlined by McCollister and French [64], to which we will apply cost estimates provided in the 2008 national survey of 110 substance abuse treatment programs by French et al., adjusted for inflation [67]). We will also collect self-reported use of other health services (e.g., dental care, primary care, chiropractor), following the approach by Bell et al., to assess the cost-effectiveness of supervised versus unsupervised buprenorphine-naloxone administration [68]. We will derive cost estimates for various types of health care use (e.g., emergency room visits, hospitalizations, primary care visits, etc.) using data from the American Hospital Association and the American Medical Association.

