Missing data. In previous addiction work, we completed 85% of surveys at 4, 8, and 12 months. We anticipate greater reductions at months 16, 20, and 24, reaching about 65% by month 24. In previous studies, we have kept missing data on core items in a survey to about 2% and expect a comparable rate in this study. In addiction treatment, data are not likely to be missing at random (i.e., the probability that data are missing is related to what the data would have been had the data been observed). For example, some patients may not want to disclose opioid use in surveys. Because this may lead to biased parameter estimates for our models, we will identify missing data patterns and use pattern-mixture modeling to test the sensitivity of our longitudinal intervention analysis to missing data assumptions [74–77] and conduct other sensitivity analyses after imputing missing data with a range of clinically plausible values based on explicit assumptions for the missing data (e.g., best-case, worst-case; with and without multiple imputation) [78–80].

Intention-to-treat and subject noncompliance. Standard intention-to-treat (ITT) estimates the average treatment effect by comparing outcomes based on assignment to treatment, but ignoring use of the treatment. Because ITT estimates do not represent treatment efficacy under noncompliance (e.g., a patient is randomized to A-CHESS but does not use the system), we will address noncompliance by also estimating treatment effects only for compliers using as-treated, per-protocol [81], and CACE (Complier Average Causal Effect) [82].

Dropout rates. In our A-CHESS RCT with alcohol-dependent patients [33], 88 patients were using opioids as well as alcohol; 261 were not using opioids. We compared the post-test survey response rate of opioid-using patients to the response rate of patients who did not use opioids. The non-opioid-using patients’ response rates were 94.3% at 4 months; 90.6% at 8 months, and 86.7% at 12 months. The opioid-using patients’ response rates were 91.2%, 86%, and 79.1%. Response rates declined in a relatively linear fashion in both groups, with reductions of about 5 percentage points in each period. We assumed a 65% response rate at 24 months by continuing the drop off rate for each of the three periods from 79% to 74% to 69% to 64%. Hence, we believe it is likely that by the end of the study we will still be able to reach 65% of patients originally enrolled.

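### The protocol wrongly lists as-treated and per-protocol analyses with CACE as estimates of the effect in compliers; both are open to selection bias on A-CHESS use

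*Protocol article*

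**What the plan says.** The point is in the Protocol article, Data analysis, paragraph on intention-to-treat and subject noncompliance. ITT is described as "comparing outcomes based on assignment to treatment, but ignoring use of the treatment". The paragraph then gives the reason for going further: "Because ITT estimates do not represent treatment efficacy under noncompliance". Its example of noncompliance is that "a patient is randomized to A-CHESS but does not use the system". The remedy is "estimating treatment effects only for compliers using as-treated, per-protocol [81], and CACE". All three methods are given the same target, with no distinction between them and no caveat on any.

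Four other places bear on this:

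- Control condition: "Patients in the control condition will receive treatment as usual including MAT".
- Smartphone distribution: "Patients randomized to MAT + A-CHESS who do not already have an Android smartphone will be given one loaded with A-CHESS". Those who already own an Android phone have the app installed. Nothing describes controls receiving A-CHESS.
- Experimental condition: disengagement is expected. "Participants whose patterns of using A-CHESS demonstrate they are likely to stop using the system will receive automated messages".
- Measures, on the earlier trial in alcohol-dependent patients: "Cumulative use (number of pages viewed and days used) significantly predicted risky drinking days".

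**The concern.** An effect in compliers compares patients who use A-CHESS when offered it with patients of the same kind who were not offered it. Controls are never offered it, so that second group exists in the control arm but cannot be seen. CACE recovers the comparison indirectly from random assignment. The other two methods do not attempt it; they select on behaviour after randomization and so mix any effect of A-CHESS with whatever distinguishes patients who keep using a recovery app.

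Such a difference is plausible here. Use is voluntary, some patients are expected to stop, relapse may itself end use, and use predicted outcome in the earlier trial. The mediation paragraph recognizes a problem of this kind: it adjusts for drug use occurring while mediators are measured, because use may depress the ratings. The noncompliance paragraph states no comparable safeguard.

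At stake is how the supplementary results are read. If ITT showed little and two further estimates, both labelled as effects in compliers, looked favourable, a reader could take selection for efficacy.

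**Working it through.** **Figures from the protocol.** Randomization is 1:1. With 35% attrition, 440 × 0.65 = 286, which reproduces the stated final N and gives 143 per arm. The design effect is a standardized difference of .35, put at about three opioid use days a month, so the implied SD is 3/.35 = 8.57 days a month.

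**Assumptions, not in the documents.** A share c of patients would use A-CHESS if offered it. Would-be non-users have an outcome worse by D than would-be users, in either arm. Controls have no access. A-CHESS has no effect. Ranges tried: c = .5 to .9 and D = −0.3 to 0.8 SD.

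**Algebra.** Set the user mean at 0 and the non-user mean at D; higher is worse.

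- Control mean: c × 0 + (1 − c)D = (1 − c)D.
- Per-protocol: users minus all controls = −(1 − c)D.
- As-treated: for each control there are (1 − c) A-CHESS-arm non-users. The comparator mean is [(1 − c)D + (1 − c)D] / [1 + (1 − c)] = 2(1 − c)D/(2 − c), and the contrast is minus that.
- ITT: (1 − c)D − (1 − c)D = 0, so CACE = 0/c = 0.

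With a true effect in users only, that effect is simply added to the per-protocol and as-treated contrasts; the selection term stays.

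**One point in days.** With c = .6 and D = 3 days a month, per-protocol shows 0.4 × 3 = 1.2 days of false benefit and as-treated 2 × 0.4 × 3/1.4 = 1.71 days. These are 40% and 57% of the three-day target.

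**Range.** False benefit in SD, with days a month in brackets (SD × 8.57). The last two columns give the share of 20,000 simulated null trials, 143 per arm, two-sided alpha .05 (assumed), with a significant benefit.

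| c | D (SD) | Per-protocol | As-treated | Per-protocol significant | As-treated significant |
|---|---|---|---|---|---|
| .5 | 0.3 | 0.15 (1.29) | 0.20 (1.71) | 19% | 32% |
| .5 | 0.5 | 0.25 (2.14) | 0.33 (2.86) | 43% | 71% |
| .5 | 0.8 | 0.40 (3.43) | 0.53 (4.57) | 83% | 99% |
| .7 | 0.5 | 0.15 (1.29) | 0.23 (1.98) | 21% | 47% |
| .9 | 0.3 | 0.03 (0.26) | 0.05 (0.47) | 4% | 6.5% |
| .9 | 0.5 | 0.05 (0.43) | 0.09 (0.78) | 6% | 12% |
| .9 | 0.8 | 0.08 (0.69) | 0.15 (1.25) | 10% | 23% |

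Throughout, ITT showed a significant benefit in about 2.5% of runs, as it should, and CACE averaged about 0. At D = 0 neither naive contrast is biased. At D = −0.3 and c = .5 both reverse, to apparent harm of 0.15 SD (per-protocol) and 0.20 SD (as-treated).

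**What CACE needs.** If assignment alone shifts non-users' outcome by δ, ITT = c × effect + (1 − c)δ, so CACE is off by (1 − c)δ/c: by δ at c = .5 and by 0.11δ at c = .9.

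**The case against.** The strongest reply is that the direction of bias is not established. The earlier-trial result concerns alcohol-dependent patients, gives no sign, and does not separate selection from effect. The reminder messages say nothing about prognosis. Some features pull the other way: the Help function, counselor contact after reported craving and coach alerts after reported use may draw higher-risk patients into use. This stands. A reader might infer that both analyses must favour A-CHESS by construction. The documents do not support that, since the bias depends on an unknown gap and can be zero or negative. Nor do both analyses use the same unselected control group: only per-protocol compares users with all controls.

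Second, these are supplements. ITT is kept, the primary hypothesis and power rest on the comparison by arm, and nothing says the other estimates would override a null ITT. This also stands, so the inference that the plan would present them as proof of efficacy goes further than the text.

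Third, the use threshold, any adjustment and the labelling in reports may sit in the full protocol or analysis plan, and the reference cited for per-protocol is not at hand. Their absence is no finding. But the article does state a target for all three methods, and that statement is wrong for two of them as ordinarily defined.

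Fourth, CACE has its own weak point. Assigned patients without an Android phone receive one with an unlimited plan for 16 months, and coaches write to those who do not log in, so assigned non-users still receive something that may affect outcome. This is a fair reason to state the exclusion restriction. It does not turn the other two contrasts into complier effects.

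**Conclusion.** The concern holds as a misstated property of two supplementary analyses. As-treated and per-protocol do not estimate the effect in compliers unless use is unrelated to prognosis, which the article does not claim. If users have the better prognosis, both could show benefit with no true effect: about 0.03-0.40 SD for per-protocol and 0.05-0.53 SD for as-treated, under assumed use of 50-90% and an assumed gap of 0.3-0.8 SD. At 50% use and a 0.5 SD gap, as-treated alone gives 0.33 SD, close to the whole design effect of .35; at 90% use the problem is small. These sizes also assume that controls have no A-CHESS. The primary comparison by assignment is untouched, and the appropriate estimator is already in the plan, so this is a correction worth making rather than a threat to the trial's main conclusion.

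**What to change.** Reword the noncompliance paragraph so that CACE, with random assignment as the instrument, is the only estimate of the effect in compliers. Define use in advance from the time-stamped A-CHESS logs. State the exclusion restriction, and say that the phone, data plan and coach messages reaching assigned non-users may strain it. Keep as-treated and per-protocol only as descriptive associations, labelled as subject to selection bias and not as evidence of efficacy, or drop them.

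The cost is small. No new data are needed and CACE is already planned. Its interval will be wider than those of the naive contrasts, and two analyses lose their standing as efficacy estimates. ITT is unchanged.

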### Randomization

The project director will use a computer-generated allocation sequence to randomize participants in a 1:1 ratio to MAT + A-CHESS or MAT alone, stratifying on gender and site and balancing on age, level of care (intensive outpatient treatment, day treatment, or weekly or monthly counseling), and whether patients had prior SUD treatment. The project director will inform the site coordinator of the group assignment by email; in the email, the participant will be identified only by study ID (the code used to make the identity of participants unknown). The site coordinator will initiate patients into the study condition and, if the patient is assigned to MAT + A-CHESS, provide training.

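### The 65% month-24 response behind N = 286 rests on a 5-point loss per period that the opioid users' own figures do not show, and the 35% attrition is credited to two different sources

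*Protocol article*

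**What the plan says.** All the relevant text is in the protocol article, Data analysis, under Power and sample size justification.

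- **Primary analysis:** "Based on data from the two sites from which most study participants will be recruited, we assume 35% attrition over the course of the study", which leaves 286 of 440. It then states that "recruitment of 440 patients will provide 80% power to uncover a standardized difference of .35 across the 24 months".
- **Dropout rates:** in the earlier A-CHESS trial in alcohol-dependent patients, the 88 opioid users' "response rates were 91.2%, 86%, and 79.1" percent at 4, 8 and 12 months. The 261 other patients had 94.3%, 90.6% and 86.7%. The decline is described as roughly linear in both groups, "with reductions of about 5 percentage points in each period". The month-24 figure is then obtained by "continuing the drop off rate for each of the three periods from 79% to 74% to 69% to 64" percent, and 65% is carried forward.
- **Missing data:** about 85% of surveys were completed at months 4, 8 and 12 in earlier work, and "We anticipate greater reductions at months 16, 20, and 24", to about 65% by month 24.
- **Secondary analyses:** the sample size is said to give 80% power for a two-tailed 16-point difference in HIV/HCV screening, with one group near 50%. The N is not given.
- **Mediation and moderation analyses:** about 220 patients are needed, and 286 is cited as sufficient.

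**The concern.** The projection starts from the opioid users' month-12 rate but then subtracts a step that is smaller than either loss that group showed between visits. Five points is close to the unweighted average of the two groups' mean losses and describes neither group. The result is a month-24 response, and hence a final N, that is more favourable than the quoted data support. The final N of 286 accompanies the primary power claim, is the stated reassurance for the process analyses, and may underlie the screening power.

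Separately, one attrition figure has two stated origins: site data that the article does not show, and an extrapolation from a trial in a different population. A reader cannot tell which one the sample size rests on.

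**Working it through.** **1. The plan's own figures.** 440 × (1 − 0.35) = 286, which reproduces. The chain is 79 − 3 × 5 = 64, and 440 × 0.64 = 281.6, about 282. Carrying 65% instead of 64% adds about 4 patients.

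**2. Observed losses per period** (from the rates in Dropout rates).

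| Group | Month 4 to 8 | Month 8 to 12 | Mean |
|---|---|---|---|
| Opioid users | 91.2 − 86.0 = 5.2 | 86.0 − 79.1 = 6.9 | 6.05 |
| Other patients | 94.3 − 90.6 = 3.7 | 90.6 − 86.7 = 3.9 | 3.8 |

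The unweighted average of the two means is (6.05 + 3.8)/2 = 4.9. Before month 4 the opioid users had already lost 100 − 91.2 = 8.8 points.

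**3. Linear continuation for three periods from 79.1%**, which is the document's own method, with N = 440 × rate.

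| Step used | Month-24 response | N |
|---|---|---|
| Mean, 6.05 | 79.1 − 18.15 = 60.95% | 268 |
| Last, 6.9 | 79.1 − 20.7 = 58.4% | 257 |
| Mean since enrolment, (100 − 79.1)/3 = 6.97 | 79.1 − 20.9 = 58.2% | 256 |
| Smallest, 5.2 | 79.1 − 15.6 = 63.5% | 279 |

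**4. Non-linear check.** A constant proportional loss gives 79.1 × (79.1/86)³ = 61.5% from the last period, 79.1 × 0.791 = 62.6% from enrolment, and 79.1 × (79.1/91.2)^1.5 = 63.9% from months 4 to 12. From months 4 to 8 alone it gives 79.1 × (86/91.2)³ = 66.3%.

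**5. Primary power, simple two-group check.** Alpha is not stated for the primary analysis, so two-sided 0.05 is assumed. With n per arm (1:1), power ≈ Φ(0.35 × √(n/2) − 1.96).

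- N = 286, n = 143: Φ(2.960 − 1.96) = 84%
- N = 268, n = 134: Φ(2.865 − 1.96) = 82% (81% with the t distribution)
- N = 256, n = 128: Φ(2.800 − 1.96) = 80%

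This does not reproduce the plan's 80%, which comes from a longitudinal program whose other inputs are not given.

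**6. Screening power, 50% versus 66%, two-sided 0.05.** Power = Φ[(0.16√n − 1.96√(2 × 0.58 × 0.42)) / √(0.50 × 0.50 + 0.66 × 0.34)].

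| N analysed | Power for 16 points | Difference detectable with 80% power |
|---|---|---|
| 440 | 93% | 13.2 points |
| 286 | 79% | 16.3 points |
| 268 | 76% | 16.8 points |
| 256 | 74% | 17.2 points |

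**The case against.** The strongest reply is that nothing the plan claims about primary power is shown to be wrong. A reader might infer that the trial is underpowered, but the documents do not support that. The simple check stays at about 80% even at N = 256. The planned mixed model also uses earlier visits from patients who later drop out, so month-24 N is not the analysed N. This stands. So does the point that the process analysis needs only about 220, which 256 exceeds.

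The range of 58% to 61% is itself soft. It rests on 88 opioid users: the month-12 rate has an approximate 95% interval of 71% to 88%, and the gap between losses of 5.2 and 6.9 points is about 1.5 patients (0.017 × 88). One proportional variant reaches 66.3%. This also stands: the figure is a planning range, not a corrected fact. It does not rescue the text, because the document states a linear decline and says that it continues the observed rate.

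A reader might also see a contradiction between the expected greater reductions after month 12 and the constant 5-point step. That sentence more naturally contrasts later completion with the 85% level at months 4 to 12. The opioid users' mean over those visits is (91.2 + 86 + 79.1)/3 = 85.4%, so the contradiction is not pressed.

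Finally, if the site data do support 35% attrition, 286 stands whatever the earlier trial shows. That is true, and it is why the two sources must be reconciled first.

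**Conclusion.** The point holds as an error in the attrition derivation together with a conflict of sources. The statement that both groups lost about 5 points per period does not fit the opioid users, and the printed chain does not reach the 65% drawn from it. If the earlier trial is the basis and the decline is linear, month-24 response is about 61% (58% to 64%, the top being the printed chain) and final N about 268 (256 to 282), which is 4 to 30 fewer than 286.

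The consequence for the primary analysis is a thinner margin, not a demonstrated shortfall. For HIV/HCV screening the answer depends on a denominator that the article never states. It would be wrong to read 286 into that sentence as fact. With all 440 analysed, the 16-point claim is met. With month-24 completers, 286 gives 79%, close to the claim allowing for rounding, and 256 to 268 gives 74% to 76%.

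**What to change.** 1. Name one source for the 35% attrition. If it is the site data, say so in Dropout rates and present the earlier trial only as support.
2. Replace the statement of about 5 points in both groups with the observed losses: 5.2 and 6.9 for opioid users, 3.7 and 3.9 for the others.
3. If the earlier trial is the basis, restate month-24 response as about 61% (range 58% to 64%) and final N as about 268 (256 to 282). Rerun the longitudinal power calculation with per-visit response rates; the mean step gives about 91, 86, 79, 73, 67 and 61%.
4. State the N behind the HIV/HCV screening power. If it is month-24 completers, restate the difference detectable with 80% power as about 17 points. If all 440 are analysed, the 16-point claim can stay.

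The cost is a recalculation and a few restated figures. This finding by itself calls for no added patients and no change to the design or the analysis.
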